#### **2. Feasibility of retaining participants in the RCT**

Defined as attrition from the research protocol of no more than 15% of randomised participants at 5 (+/-1) months.

If these are met the full trial will go ahead. If these are not met overall, but are met in the last half of the pilot trial after trial procedures have been improved based on lessons learned from the early stage of the pilot trial, then the full trial will go ahead.

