#### 8.1.2 Sample size

The sample size for a feasibility study should be adequate to estimate the uncertain critical parameters (standard deviations for continuous outcomes; consent rates, event rates, attrition rates for binary outcomes) needed to inform the design of the full RCT with sufficient precision [37, 58–60]. For the main RCT, the target sample size is 688 participants (344 per arm). We are proposing that 15 CF units recruit on average 46 patients in six months, a recruitment rate of approximately eight patients per centre per month.

To assess whether this recruitment rate is feasible the external pilot RCT will open in two CF units for 12 months, with four months recruitment, one months 'run-in' period (the period between the consent and baseline visit), and 5 (+/-1) months follow up. To match the proposed recruitment rate of the main RCT, the target sample over the four months for which the pilot RCT is open, will be 32 per centre (64 in total from the two pilot centres). We propose to recruit to time, that is for a fixed period of four months rather than to a fixed sample size. We would want to see a minimum of 75% of the recruitment target to be confident of the trial viability i.e. at least 48 patients in total consented and randomized in four months' of recruitment from two centres.

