## 11. Data analysis

### 11.1 Quantitative analysis

The analysis will be performed after data lock by a CTRU statistician under the supervision of the senior study statistician. As the trial is a pragmatic parallel group RCT data will be reported and presented according to the CONSORT 2010 statement [61] with reference to proposed extension for pilot / feasibility studies [37]. As a pilot/feasibility study the main analysis will be mainly descriptive and focus on confidence interval estimation and not formal hypothesis testing [58]. We will report rates of consent, recruitment and follow-up by centre and by randomized group.

Clinical outcome measures will be summarised overall and by randomized group. Baseline demographic (age, gender), physical measurements (e.g. weight, height, BMI), and patient reported outcome measures (EQ-5D, PAM-13, Assessment of Routine, MAD-3, SRBAI, CFQ-R, GAD-7, COM-BMQ, PHQ-8), and clinical measurements (e.g. FEV1, IV days in last registry year ) will be described and summarised overall and for both treatment groups.

The primary outcome is the number of pulmonary exacerbations treated with IV antibiotics over the 6 month post-randomisation follow-up period. We will also include, as part of the feasibility analysis, estimation of the effect size for the 6-month pulmonary exacerbations outcome with 95% confidence interval estimates to check that the likely effect is within a clinically relevant range (as confirmation that it is worth progressing with the full trial). For this we will use a Poisson generalised linear model (GLM). Secondary continuous outcomes such as six-month post randomisation FEV1, BMI EQ-5D, PAM-13, Assessment of Routine, MAD-3, SRBAI, CFQ-R, GAD-7, COM-BMQ, PHQ-8) will be analysed with a multiple linear regression model with the baseline value of the outcome and randomised group as covariates. The treatment group coefficient and its associated 95% confidence interval will be reported from the various multiple linear regression models. The mean level of adherence (to prescribed medication) between the intervention and control groups over the 6 month post-randomisation follow-up period will also be reported and compared between the groups and a 95% confidence interval (CI) for the mean difference in this parameter between the randomised groups will also be calculated.

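### The pilot's exacerbation estimate is offered as confirmation for the full trial, which 24–32 per arm cannot give, and its plain Poisson interval makes no allowance for over-dispersion or unequal follow-up

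*Protocol*

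**What the plan says.** Section 11.1 describes the pilot analysis as mainly descriptive, with a "focus on confidence interval estimation and not formal hypothesis testing". It then plans "estimation of the effect size for the 6-month pulmonary exacerbations outcome with 95% confidence interval estimates", and gives the purpose as "to check that the likely effect is within a clinically relevant range (as confirmation that it is worth progressing with the full trial"). The model is fixed in one sentence: "For this we will use a Poisson generalised linear model (GLM"). No dispersion parameter, robust variance, offset or covariate is attached to it.

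The sample size in Section 8.1.2 follows from "a recruitment rate of approximately eight patients per centre per month". The target is "32 per centre (64 in total from the two pilot centres") and the minimum is "at least 48 patients in total consented and randomized in four months' of recruitment from two centres". No exacerbation rate, variance or target effect appears.

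Section 7.1 sets out the stop-go criteria, covering recruitment and retention, and says of them: "If these are met the full trial will go ahead". The objectives in Section 3.2 add quality of primary outcome data. None of these is about efficacy.

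**The concern.** There are two separate points.

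The first is the use made of the estimate. A pilot sized on recruitment rate is asked to show that the effect lies in a clinically relevant range that is never defined. Section 7.1 then gives that check no role. If recruitment and retention succeed but the estimate looks unfavourable, or the reverse, the protocol does not say what follows. At stake is a nearly uninformative estimate being reported as support for the full trial, or as evidence against it.

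The second is the interval itself. A Poisson model sets the variance equal to the mean. Exacerbations recur in the same people, and randomisation is stratified by IV antibiotic days in the previous 12 months (Section 9.1), so variance above the mean is likely and the interval would then be too short. The plain model also assumes away the dispersion, although Section 8.1.2 says the pilot should estimate the parameters needed to design the main trial.

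**Working it through.** **Sample size.** 2 centres × 4 months × 8 per month = 64, and 0.75 × 64 = 48. Both stated figures reproduce. Equal allocation (Section 9.1) gives 32 or 24 per arm.

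**Event rate (assumed; the protocol states none).** Section 2.1 gives 171,907 IV days in 2012 and 10,000 people with CF. At an assumed 14 days per course:
- 171,907 / 10,000 / 14 = 1.228 courses per person-year.
- × 5/12 = 0.51; × 6/12 = 0.61 per person.
- Events per arm: 24 × 0.51 = 12.2 up to 32 × 0.61 = 19.5, so about 12–20.

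**Width if Poisson is exactly right.** With E events in each arm, the 95% limits are the rate ratio ×/÷ exp(1.96 × √(2/E)).
- E = 12: factor 2.23.
- E = 20: factor 1.86.

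An observed ratio of 0.8 would thus carry an interval of about 0.36–1.78 (E = 12) or 0.43–1.49 (E = 20).

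**Sensitivity to the event rate.** The lay summary says almost 6,000 of the 10,000 are adults. Attributing every IV day to adults, which is an upper extreme, gives 171,907 / 6,000 / 14 = 2.05 per year, or 0.85–1.02 in 5–6 months. That is 20.5–32.7 events per arm and factors of 1.85–1.62. At 1.62, an observed 0.8 still spans 0.49–1.30. In the most favourable case tried (32 per arm, 1.5 events each, pure Poisson), an observed 0.75 gives 0.50–1.12.

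**Simulation with pure Poisson counts** (24 and 32 per arm, means 0.51 and 0.61, log rate ratio with standard error √(1/A + 1/B), where A and B are the arm totals):
- True ratio 0.8: the point estimate exceeds 1 in about 23–27% of trials.
- True ratio 1.0: about 88–91% of intervals contain both 0.8 and 1.0.

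**Coverage under over-dispersion.** The counts were negative binomial with variance = φ × mean, 24–32 per arm, means 0.51–1.0 and a true ratio of 1. The values of φ are assumed. As an illustration, two equal strata with rates 0.2 and 1.0 have mean 0.6 and variance 0.6 + 0.16 = 0.76, so φ = 0.76 / 0.6 = 1.27.

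| φ | Poisson 95% CI | Robust SE |
|---|---|---|
| 1.27 | 92–93% | about 95% |
| 1.5 | about 90% | about 94% |
| 2.0 | 84–85% | 93–94% |

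At φ = 2 the honest factor is exp(1.96 × √(4/E)), which is 3.10 at E = 12 and 2.40 at E = 20.

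**Time at risk.** Section 7.4.1 counts events over 5 (±1) months after baseline, while Section 11.1 uses 6 months after randomisation. Individual follow-up can run from 4 to 6 months, a ratio of 1.5, and the model as written has no offset.

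**The case against.** The best defence is that the analysis is labelled descriptive, that Section 7.1 makes the effect no gate, and that one sentence naming a model family leaves offset, covariates and variance estimator to the SAP, which was not available for this review. Poisson with robust standard errors is still a Poisson GLM, so an SAP could repair the interval without contradicting the protocol. This lowers the severity and weakens the modelling half. It does not touch the confirmation clause, which is protocol text and assigns the estimate a task that it cannot do under any dispersion.

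Four stronger readings are tempting but not supported:
- A reader might infer that the interval certainly lacks 95% coverage. The protocol gives no dispersion figure. At φ = 1.27 the loss is only 2–3 points, and adjusting for the stratum would recover the part due to strata.
- A reader might infer that the trial stratifies because rates differ widely. Section 9.1 gives the cut-point and no reason.
- A reader might infer that nearly every interval will include both large benefit and harm. Taking those as 0.5 and 1.25, only about 32–64% of pure Poisson intervals contain both, at the assumed rates and a true ratio of 1.0 or 0.8.
- A reader might infer that a poor estimate could stop the full trial. Section 7.1 contains no such rule, although it does allow for the funder's perspectives.

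The event rate is also rough: it includes children and treats every IV day as part of a qualifying 14-day course. The sensitivity range above shows that the conclusion survives.

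**Conclusion.** The concern holds at moderate severity. Its main part needs no dispersion assumption: with 24–32 per arm and about 0.5–0.6 events each, a correct Poisson interval still spans the rate ratio ×/÷ about 1.9–2.2, and higher plausible event rates do not rescue it. The wording in Section 11.1 promises confirmation that the design cannot deliver, against a range that is not stated, and it sits apart from the go rule in Section 7.1. The second part is conditional. If counts are over-dispersed, as is likely for recurrent events, the plain Poisson interval is too narrow, by an amount that the documents do not let us fix. The two parts are independent: correcting the variance makes the interval honest but no more able to guide progression.

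**What to change.** 1. In Section 11.1, specify a negative binomial model, or Poisson with robust standard errors, with log time at risk as offset. Reconcile the follow-up period with Section 7.4.1. Report the event rate and dispersion estimate for main-trial planning.
2. Delete the clause that offers the estimate as confirmation for the full trial. State that the rate ratio and its interval are descriptive and are not a progression criterion.

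The change is to wording only. The cost is a wider reported interval (about 1.1–1.7 times as wide on the log scale in simulations with negative binomial dispersion k of 0.5–1.5) and the loss of an efficacy check that the pilot could not perform.

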| Confirmation of eligibility form                                                                                                                                                                                                                                                                                                                                                                              | Prospect | Site          | ●             | -                             | -                | -                     | -                                         | -                                 |
| Informed consent                                                                                                                                                                                                                                                                                                                                                                                              | Prospect | Site          | ●             | -                             | -                | -                     | -                                         | -                                 |
| Intravenous days in last registry year                                                                                                                                                                                                                                                                                                                                                                        | Prospect | Site          | ●             | -                             | -                | -                     | -                                         | -                                 |
| Pseudomonas status +                                                                                                                                                                                                                                                                                                                                                                                          | Prospect | Site          | ●             | -                             | -                | -                     | -                                         | -                                 |

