## 9. Assignment of interventions

### 9.1 Sequence generation

Participants will be allocated in equal proportions to one of the two groups using a computer generated pseudo-random list, stratified by centre and the number of days participants have been on IV antibiotics in the previous 12 month period as collected at consent visit, with random permuted blocks of varying sizes. The two categories for stratification within the number of IV days will be (i) less than or equal to 14 days and (ii) greater than 14 days.

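### The linear models for secondary continuous outcomes omit the randomisation stratifiers, and the IV-days stratifier is given two reference periods (minor)

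*Protocol*

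**What the plan says.** **Randomisation.** Protocol section 9.1 allocates 1:1 in permuted blocks, "stratified by centre and the number of days participants have been on IV antibiotics in the previous 12 month period". The two IV-days categories are "i) less than or equal to 14 days and (ii) greater than 14 days".

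**Secondary continuous outcomes.** Section 11.1 fits each with a "multiple linear regression model with the baseline value of the outcome and randomised group as covariates", and reports the group coefficient with its 95% confidence interval.

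**Exacerbations and adherence.** For exacerbations, section 11.1 says "For this we will use a Poisson generalised linear model (GLM") and names no covariates. Adherence is compared by a mean difference with a 95% interval, again with no covariates named.

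**IV-days variable.** Section 9.1 refers to "the number of days participants have been on IV antibiotics in the previous 12 month period as collected at consent visit". The only IV-days item that Table 3 schedules at the consent visit is "Intravenous days in last registry year", and section 11.1 summarises "IV days in last registry year" at baseline.

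**Role of the intervals.** Section 11.1 describes a largely descriptive analysis based on interval estimation rather than testing. Section 8.1.2 says that a feasibility study should estimate standard deviations well enough to inform the full trial.

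**The concern.** Stratified allocation balances the arms on centre and prior IV days, so differences between strata largely drop out of the treatment contrast. A linear model without those factors leaves the same differences in its residual variance. The reported standard error is then larger than the design warrants, and so is the residual SD carried forward.

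The usual answer, that covariates can wait for the statistical analysis plan, does not fully serve here. The protocol gives the linear model a closed list, so a plan that added the stratifiers would depart from it.

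The second issue is that one label for the stratifier covers the 12 months before consent and the other covers a registry year. If those periods differ, a participant could be randomised in one IV-days category and described, or adjusted for, in the other.

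**Working it through.** **1. The plan's own figures.** Two centres × 4 months × 8 per month = 64, and 0.75 × 64 = 48. Both match section 8.1.2 and are the two sample sizes used below.

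**2. Linear model: assumed inputs.** The protocol gives no stratum effects, so these are assumptions. Strata are split 50:50. The within-stratum outcome SD is 1. The slope on the baseline value is 0.6, leaving a residual variance of 1 − 0.36 = 0.64 once strata are fitted. Mean baseline differs by 0.5 between IV-days categories. The residual IV-days effect is d (in SD units, beyond baseline) and the centre effect is d/2. There is no treatment effect.

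**3. Linear model: formula.** With the strata omitted, the residual variance gains the part of their effect that baseline does not absorb.

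- IV days: variance 0.25, less 0.125²/1.0625 = 0.0147 explained by baseline, leaves 0.2353.
- Centre: 0.25 × (1/2)² = 0.0625.
- Residual variance without strata = 0.64 + 0.2978 d².

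| d (SD) | Variance without strata | SD without / with strata | Excess |
|---|---|---|---|
| 0.3 | 0.6668 | 0.817 / 0.800 | 2.1% |
| 0.6 | 0.7472 | 0.864 / 0.800 | 8.0% |
| 1.0 | 0.9378 | 0.968 / 0.800 | 21% |

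**4. Linear model: simulation.** 1,500 trials per setting, with permuted blocks of 2 or 4 within centre × IV-days strata.

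| N | d | Mean CI width without / with strata | Ratio | Coverage without / with strata |
|---|---|---|---|---|
| 48 | 0 | 0.933 / 0.936 | 0.997 | 95.5% / 95.3% |
| 48 | 0.3 | 0.958 / 0.941 | 1.018 | 95.7% / 95.3% |
| 48 | 0.6 | 1.008 / 0.934 | 1.079 | 97.0% / 95.3% |
| 48 | 1.0 | 1.132 / 0.935 | 1.211 | 98.0% / 94.5% |
| 64 | 0 | 0.803 / 0.804 | 0.999 | 95.2% / 95.2% |
| 64 | 0.3 | 0.820 / 0.805 | 1.019 | 94.8% / 94.5% |
| 64 | 0.6 | 0.869 / 0.805 | 1.080 | 96.3% / 95.0% |
| 64 | 1.0 | 0.973 / 0.804 | 1.210 | 97.7% / 94.8% |

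The simulation agrees with the formula. The Monte Carlo error on coverage is about √(0.95 × 0.05/1500) = 0.6 percentage points, so at 0.3 SD the coverage shift cannot be told from zero. If the strata carry no information (d = 0), including them widens the interval by at most 0.3%.

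**5. Poisson model.** Without covariates, the model-based standard error of the log rate ratio is √(1/E₁ + 1/E₀), where E₁ and E₀ are the event totals in the arms. Balanced strata barely alter it. In 1,000 simulated trials per setting (assumed base rate 0.4, centre rate ratio 1.3, IV-days rate ratio 4, no extra variation), interval widths without and with strata were 1.078 and 1.079 at N = 48, and 0.928 and 0.928 at N = 64. Over all settings run, including some with extra-Poisson variation, the difference was below 0.3% and coverage was nearly the same either way.

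**6. IV-days period.** Other parts of the protocol do not settle the difference. The registry extraction in section 10.1.1 covers the preceding 12 months, but for exacerbations. The resource-use form (section 7.4.2) includes inpatient IV days, but Table 3 schedules it only at 5 months. Section 9.3 mentions only basic demographic data being entered at randomisation. The registry year is not defined, so no misclassification rate can be calculated.

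**The case against.** **The loss is small and in the safe direction.** This stands. There is no bias and no undercoverage, and the baseline value may already absorb much of the IV-days signal. The stop-go criteria set out in section 7.1 concern recruitment and retention, so none turns on these secondary intervals. An excess near 21% needs a residual effect of a full SD after baseline adjustment, which is an extreme assumption.

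**Silence is not exclusion.** This also stands, for exacerbations and adherence. A reader might infer that every outcome model leaves out the strata; the text supports this only for the secondary linear models. A reader might also infer that adjustment would narrow the exacerbation interval by 11% to 19%. That figure comes from assumed stratum rates giving a dispersion of 1.27 to 1.52 (1/√1.27 = 0.89, 1/√1.52 = 0.81), and it requires an unadjusted standard error corrected for dispersion. The protocol names a plain Poisson model and plans no such correction.

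**The two IV-days labels may describe one item.** This is possible, because section 9.1 says the stratifier is collected at the consent visit and Table 3 lists a single IV-days item there. But nothing equates the two periods, so the wording still needs reconciling. A reader might infer that the mismatch undermines the randomisation. It does not, since allocation within whichever strata were used remains valid.

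**Conclusion.** The point holds as a minor one. The stated model for the secondary continuous outcomes omits both stratification factors. Under assumed residual IV-days effects of 0.3 to 0.6 SD, with a centre effect half as large, its 95% intervals are about 2% to 8% too wide at N = 48 to 64. The residual SD is overstated by the same proportion relative to a stratum-adjusted analysis. Whether that carries into the main trial depends on its analysis model, which the protocol does not give.

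No precision loss is established for the exacerbation model. The IV-days discrepancy is a real inconsistency of wording, of unknown practical size, that affects description and covariate definition rather than the validity of allocation. The statistical analysis plan was not available for this check.

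**What to change.** - In section 11.1, add centre and the IV-days category as used at randomisation to each secondary linear model, alongside the baseline value.
- Choose one IV-days period and use it in section 9.1, Table 3, section 11.1 and the randomisation system, so that the stratum, the baseline description and the covariate are the same quantity. If randomisation has already begun, record which period was actually used.
- In the statistical analysis plan, state which covariates the Poisson model and the adherence comparison will include.

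The cost is two model terms (residual degrees of freedom fall from 61 to 59 at N = 64, or from 45 to 43 at N = 48) and a wording change. No new data are needed and the sample size is unaffected.

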Further analyses with the objective nebuliser data will be performed to explore the process of habit formation with the delivery of the adherence intervention. The analyses will include:

- (a) generating objective habit scores by taking into account time of nebuliser use
- (b) using statistical process control to identify when periods of stability is achieved
- (c) other time-series methods, including cross-correlation between habit scores and adherence.

Adverse events will be based on serious adverse events (SAE) case report forms. A serious adverse event is defined as any adverse event or adverse reaction that results in death, is life-threatening, requires hospitalisation or prolongation of existing hospitalisation, results in persistent or significant disability or incapacity, or is a congenital anomaly or birth defect.

The following summaries will be presented as overall rates and stratified by AE classification:

- the number and percentages of patients reported as having Serious Adverse Events (SAE) in each treatment arm; and,
- the number and percentages recorded as having all forms of Adverse Events (AE) in each arm.

This information along with the acceptability of the study design and protocol to patients/GPs; the safety of the intervention; patient recruitment and attrition/retention rates will enable us to determine whether or not the definitive RCT is feasible within a satisfactory timescale and cost envelope using UK centres alone.

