## 12.3 Harms (safety assessments)

### 12.3.1 Serious Adverse Events

Trial sites are to report Serious Adverse Events (SAEs) in conjunction with the CTRU standard operating procedure PM004 (Adverse events and serious adverse events). The definition of an SAE is as follows:

- results in death;
- is life-threatening\* (subject at immediate risk of death);
- requires in-patient hospitalisation or prolongation of existing hospitalisation;\*\*
- results in persistent or significant disability or incapacity;
- consists of a congenital anomaly or birth defect; or,
- is another important medical event that may jeopardise the subject.\*\*\*

\* 'life-threatening' refers to an event in which the patient was at risk of death at the time of the event; it does not refer to an event which hypothetically might have caused death if it were more severe.

\*\*Hospitalisation is defined as an inpatient admission, regardless of length of stay, even if the hospitalisation is a precautionary measure for continued observation. Hospitalisations

for a pre-existing condition, including elective procedures that have not worsened, do not constitute an SAE.

\*\*\*Other important medical events that may not result in death, be life-threatening, or require hospitalisation may be considered a serious adverse event/experience when, based upon appropriate medical judgment, they may jeopardise the subject and may require medical or surgical intervention to prevent one of the outcomes listed in this definition.

It is not anticipated that there will be many SAEs related to the behaviour change intervention. We will report any SAEs which are deemed related to the trial intervention and unexpected to the Sponsor within the specified timeframes below (12.3.4).

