### **12.3.2 Adverse events we require reporting:**

We do require that sites report any new diagnosis of depression which requires treatment with medication or psychological therapy e.g. Cognitive Behavioural Therapy (CBT).

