### 12.3.4 Reporting

Adverse events and SAEs can be reported for participants at any stage of their trial participation. A member of the site study team (interventionist, clinician or other) will enquire about any adverse events at routine clinic appointments. These will be recorded on the adverse event section of the paper CRF and database. The event will be assessed by the local Principal Investigator and the form will be kept in the site file. Serious adverse events will be reported in the periodic safety reports to the research ethics committee and Trial Steering committee.

All adverse events (serious or other based on the definitions above) will be recorded on the case report form and details will be **entered on the study database within 1 week of completing the paper form**. Any SAEs which are deemed related to the trial intervention, the site will complete the paper CRF and **fax details this form to the CTRU within 24 hours of becoming aware of the event** in order for the CTRU to report this event to the Sponsor and the main REC within the required timeframes (15 days).

In participants using the Bi-Neb, any Adverse or SAEs relating to the use of Promixin via this device will be reported to the Patient Support team (PSP) at Phillips as per their standard practice.

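### Section 11.1 names SAE forms as its adverse-event source, which cannot supply the by-arm table of all adverse events it promises; non-serious treated depression is at risk of being left out

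*Protocol*

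**What the plan says.** Section 11.1 (Quantitative analysis) opens its safety paragraph with "Adverse events will be based on serious adverse events (SAE) case report forms". It then defines a serious adverse event and lists two planned summaries. The first counts participants with an SAE in each arm. The second, which is wider, is to give "the number and percentages recorded as having all forms of Adverse Events (AE) in each arm". It ends by naming the safety of the intervention among the things that will inform whether the definitive trial is feasible.

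Section 12.3.2 lists one event for required reporting: "We do require that sites report any new diagnosis of depression which requires treatment with medication or psychological therapy".

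Section 12.3.4 covers collection. A member of the site team "will enquire about any adverse events at routine clinic appointments". On where the answers go, it is specific: "These will be recorded on the adverse event section of the paper CRF and database". It adds that "All adverse events (serious or other based on the definitions above) will be recorded on the case report form", with later entry on the study database. It also allows events to be reported throughout a participant's time in the trial.

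Table 3 has a single row for adverse events, covering other SAEs. The row is marked at clinic visits and at the 5-month visit and is blank for the period up to 30 April 2017. Section 6.4.4.6 lists what continues to be collected after the final research visit: adherence data, exacerbations, FEV1 and the subjective adherence question. SAEs are not on that list.

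**The concern.** The source named in 11.1 and the second summary promised in 11.1 do not fit together. A form completed only for serious events cannot yield a count of participants with any adverse event. Someone programming the tables from the source sentence would produce two tables with the same content and leave unused the non-serious events that sites had recorded.

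New depression needing treatment is the event most exposed. The protocol singles it out for reporting, and starting medication or psychological therapy for it need not meet any seriousness criterion. If the source sentence governs, such a case is asked about, recorded and entered on the database, but is missing from the comparison by arm.

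The 11.1 summary is the only tabulation of adverse events by arm that the protocol describes. Section 12.1 treats the study as low risk and convenes no data monitoring committee, and the periodic safety reports in 12.3.4 refer to serious events.

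**Working it through.** No calculation applies to the main point, because the protocol gives no adverse-event rate. The check sets the sections side by side.

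1. **Source named for analysis (11.1):** SAE case report forms.
2. **Tables promised (11.1):** (a) participants with SAEs by arm; (b) participants with any form of AE by arm.
3. **Can the source supply the tables?** Table (a): yes. Table (b): only its serious part.
4. **Where non-serious events are held (12.3.4):** the adverse event section of the paper CRF, then the database. A suitable source for (b) therefore exists, but 11.1 does not name it.
5. **Reading A, source sentence governs:** every event in (b) comes from an SAE form, so (b) has the same content as (a). Non-serious treated depression is not counted.
6. **Reading B, second summary governs, using the source in 12.3.4:** (b) includes non-serious events, and treated depression is counted.
7. **Which one does the text choose?** Neither. The source sentence is explicit and supports A. The second summary would be redundant under A, which supports B.

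A related mismatch bears on step 5. Section 12.3.1 counts as serious an event that "is another important medical event that may jeopardise the subject"; the definition repeated in 11.1 leaves this category out. A depression case judged serious on that ground would be an SAE under 12.3.1 but not under the definition in 11.1.

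For the secondary point, the time between the final research visit and study close follows from the protocol's own dates:

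- Anticipated first enrolment is 2 May 2016 (Appendix 1). Four months of recruitment (8.1.2) runs to about 2 September 2016.
- The final research visit is 4 to 6 months after consent (6.4.4.6).
- Longest interval: 2 May 2016 + 4 months = 2 September 2016; to 30 April 2017 is about 8 months.
- Shortest interval: 2 September 2016 + 6 months = 2 March 2017; to 30 April 2017 is about 2 months.

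During these 2 to 8 months, participants remain in the study (6.4.4.6), and those who opted in continue with the intervention (footnote to Table 4). Neither Table 3 nor 6.4.4.6 schedules SAE collection for this period, while 12.3.4 allows reporting. This is the length of a period, not a count of missed events.

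**The case against.** The strongest reply is that the protocol nowhere says SAE forms are the sole source. The second summary is a commitment in its own right, and 12.3.4 provides the data for it. A sensible analyst would draw on the database and count treated depression. This stands, and it is why the omission is one reading and not a settled outcome. A reader might infer that depression will show as zero in both arms whatever happens; the document does not support that. It does not dispose of the point, because the source sentence is still wrong for the table beneath it.

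A second reply is that depression is also followed by other means: PHQ-8 at consent and 5 months with an adjusted comparison by arm, concomitant medications at both visits, and interviews on perceived harms. This is fair, but none of them is a count of new treated diagnoses by arm.

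A third is that Table 3 proves nothing about collection. A reader might infer from the blank SAE cell that SAEs go uncollected after the final visit. The document does not support that either: objective adherence is blank in the same column, although 6.4.4.6 and Table 4 say that adherence data continue to that date. What stands is an inconsistency in the schedule.

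Fourth, 12.3.4 qualifies its recording rule by reference to preceding definitions, so it is less than clear whether depression is the only non-serious event in scope. That is correct, and this point does not depend on it.

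Finally, safety is not one of the stop-go criteria in 7.1. That limits the consequence, but 11.1 still lists safety among the inputs to the feasibility decision.

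**Conclusion.** The point holds as a contradiction: within 11.1, between the source sentence and the second summary, and between 11.1 and sections 12.3.2 and 12.3.4. Taken literally, 11.1 would omit every non-serious event, including treated depression that is not serious, from the all-AE table. On the other available reading, those events are included. The loss is therefore a risk whose realisation depends on which sentence the analyst follows.

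No numerical size can be given. The protocol states no incidence of treated depression, and multiplying an assumed rate by the target sample would show only the assumption. The conclusion rests on the current wording of the protocol. The statistical analysis plan, which is not available here, may name the right source, but the protocol sentence would still need correcting to agree with it.

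The gap in the schedule up to 30 April 2017 is secondary. It calls for reconciliation and does not show that safety data would go uncollected.

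**What to change.** Change the source sentence in 11.1 so that adverse-event summaries draw on the adverse event section of the CRF and the study database as well as the SAE forms. The all-AE summary by arm will then include depression reported under 12.3.2. Whether depression gets its own row or an interval is a matter for the table shells. While the paragraph is open, bring its SAE definition into line with 12.3.1.

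Secondarily, reconcile Table 3 and the list in 6.4.4.6 with 12.3.4. Either show adverse-event collection up to 30 April 2017 in both places, or state in 12.3.4 when reporting ends.

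The main change costs one sentence and needs no new data, since 12.3.4 already has sites record these events. The secondary change is one table cell and one list entry, or one sentence in 12.3.4.
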